Current PrU prevention repositioning protocols (derived from two small 1962 studies [18]) recommend repositioning residents at moderate, high, and severe-risk every 2 h. With VE surfaces, it may be possible to reduce repositioning frequency by extending the repositioning interval (time elapsed between scheduled repositioning of residents) from 2 to 3 or even 4 h without an increase in PrU development. In the last decade, only two studies have examined repositioning protocols. One study reported fewer PrUs in residents using VE surfaces with a 4-h repositioning interval than in residents who used non-VE surfaces with more frequent repositioning [19, 20]. The second study, Turning for Ulcer ReductioN (TURN) trial, found no significant differences in PrU incidence between 2, 3, or 4-h repositioning intervals in a sample of moderate and high-risk residents using VE surfaces. In these two studies, 90% of all new PrUs occurred within the first 15 days [20]. However, new PrUs cannot be attributed to any single factor [21], and these analyses did not comprehensively examine changes in residents’ PrU risk levels or their physiological and disease factors (medical severity).

We will examine the effects of repositioning frequency (using assigned repositioning intervals of 2, 3, or 4 h) on residents at low, moderate, and high risk of developing PrUs (Braden Scale score 10-23) and will explore the effects of risk level and medical severity individually and in combination over a 4-week intervention period. Residents deemed to be at low risk are not commonly studied, but they too develop PrUs [2, 14–16] and are therefore included in this study. An FDA-cleared patient monitoring (PM) system using individual wireless tri-axial accelerometer sensors will record resident position and movement, automate repositioning schedules, provide visual cues to nursing staff [22] via electronic display screens at the nursing station and unit hallway(s) that indicate when each resident needs repositioning, and confirms completion of repositioning. This system provides a timestamp that repositioning occurred and addresses concerns about nursing electronic medical record (EMR) documentation compliance.

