### Risk and challenges

This study design includes NHs with the same corporate management to ensure that the same standard-of-care protocols are in place in each NH. A major challenge for NH research is the potential for staff turnover. Using a successful strategy from our prior studies [31], we secured a written commitment that the study will continue even if there is a change in one or more of corporate administrative leaders for the NH system. We also have designed the study to be robust to staff turnover and potential staff resistance to a new repositioning schedule, by incorporating mandatory training with supplemental on-site instruction as needed and also incorporating training into the NH’s new staff orientations. Another potential challenge is staff inconsistency in implementing the repositioning protocol standard-of-care; consistency in repositioning is important to being able to subsequently demonstrate that the repositioning at the assigned interval actually occurred [33]. In fact, in practice, extended repositioning intervals already are thought to be extended beyond 2 h [34, 35] and there are longstanding concerns that nursing staff documentation may be unreliable for use as evidence of repositioning [20, 31, 36, 37]. The PM system monitoring capabilities will enable concerns about repositioning protocol compliance and documentation to be addressed via time-stamped tracking of identified position changes.

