##### Statistical power.

According to previous research, the average PrU incidence rates range from 5.2–15%. At the time of study design, the nine NHs within the NHS were identified with the highest PrU incidence rates which averaged 9.2% (SD = 3.3%). In power analyses, we used 3.5% for PrU incidence as the expected rate for intervention since it is the highest rate found in the TURN study (for moderate-risk patients). The PrU incidence rates have been translated into an odds ratio of 0.38 (= 3.5%/9.2%) as the effect size to detect. For Aim 1, odds ratios from a logistic regression of PrU incidence rates in the three treatment arms (i.e., at 2-, 3-, and 4-h repositioning frequencies), controlling for risk level, are proposed to test the difference in PrU incidence rates between the 4-h arm and the 2-h arm as well as between the 4-h arm and the 3-h arm at 4 weeks; we are assuming that the distance between the 2-h arm and the TURN 3-h odds ratio will be larger. A sample size of *N* = 951 (*n* = 317 for each arm) will be required to detect an odds ratio of .38 with a power of 0.95 at a one-tailed significance level of α = 0.05, according to G*Power. We are using a power of 0.95 instead of the conventional power of 0.80 to ensure that we will have a smaller Type II error to test the hypothesis of no-group difference that we expect to fail to reject. We are using a one-tailed test since we are only interested in determining whether the PrU rate is higher for assigned repositioning intervals longer than the current 2-h standard practice.. For Aim 2, GEE is proposed. A sample size of *n* = 114 for each group (total *N* = 342) will be required to detect an effect size of 5.7% (= 9.2% - 3.5%) with a power of 0.80 at a one-tailed significance level of α = 0.05, using the algorithms GEESIZE developed by Dahmen, et al., on an autoregressive structure for residual correlations [48]. Since the nine NHs will be randomly assigned to the three treatment arms, risk level will be the only potential covariate to be controlled in the models, and this is already considered in the power analyses. Therefore, we will target a sample size of *N* = 951 (the larger of the two required sample sizes) for both aims while taking into account potential losses due to turnover, attrition, and exclusion criteria. While this proposed study may look like a non-inferiority or equivalence trial, we will run regular one-tailed superiority tests, because (as noted earlier) we are only interested in examining whether or not the PrU rate is higher for less frequent repositioning than for the standard 2-h repositioning. (We assume that 2-h repositioning was followed to produce the 9.2% average PrU incidence rate across our 9 study NHs, because that is the current standard of care). Also, according to Snapinn [49], non-inferiority trials have many controversial assumptions and limitations that need to be made or addressed, and that is beyond the control of our study. For incidence, it is difficult to specify a non-inferiority margin for PrU rates. Instead, we will test the hypothesis of no group-difference by examining whether the 95% confidence intervals of the odds ratios (for Aim 1) or the PrU rates (for Aim 2) of the two pairs of compared groups (e.g., 4-h arm vs. 2-h arm and 4-h arm vs. 3-h arm) overlap. If the confidence intervals do overlap, the hypothesis for no-group difference will be confirmed.

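### The stated 0.95 power is for a ratio below 1 (3.5% against 9.2%), while the one-tailed test looks only for more ulcers at intervals longer than 2 h

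*Protocol article*

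**What the plan says.** All the sizing statements are in the Statistical power section of the protocol article.

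- **Effect size:** "The PrU incidence rates have been translated into an odds ratio of 0.38 (= 3.5%/9.2%) as the effect size to detect". The 3.5% is taken from the TURN trial and described only as what is expected under the intervention. It is not assigned to the 3-h or the 4-h arm.
- **Meaning of 9.2%:** "We assume that 2-h repositioning was followed to produce the 9.2% average PrU incidence rate across our 9 study NHs".
- **Contrasts:** 4-h against 2-h, and 4-h against 3-h.
- **Sample size:** 951 residents, 317 per arm, which "will be required to detect an odds ratio of .38 with a power of 0.95 at a one-tailed significance level of α = 0.05".
- **Direction:** the single tail is justified because "we are only interested in determining whether the PrU rate is higher for assigned repositioning intervals longer than the current 2-h standard practice". The same reason is given again beside the statement that "we will run regular one-tailed superiority tests".
- **Use of the power:** 0.95 was preferred to 0.80 so that the Type II error would be small when, as the authors expect, the hypothesis of no difference is not rejected.

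The Risk and challenges section adds that "in practice, extended repositioning intervals already are thought to be extended beyond 2 h".

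**The concern.** The trial asks whether longer intervals lead to more ulcers. In the 4-h against 2-h contrast, a ratio of 0.38 with 9.2% at 2 h describes a 62% relative reduction (1 − 0.38) at the longer interval. The declared test rejects only for an increase, so effect and test point in opposite directions.

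The other reading of 3.5% does not help. All three arms use viscoelastic mattresses, sensor cueing and the same staff training (opening of Methods; The intervention; The patient monitoring (PM) system). If 3.5% is the rate under that shared package, the gap to 9.2% compares past practice with the package. No arm-to-arm test estimates that.

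What is at stake is how a non-significant result will be read. The section relies on the 0.95 to support an expected finding of no difference. A reader would take it to mean at most a 5% risk of missing harm, and no figure in the document supports that.

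**Working it through.** **Inputs (Statistical power section):** 9.2%; 3.5%; ratio 0.38; 317 per arm, 951 in total; one-tailed 0.05; power 0.95. The section gives no clustering allowance, so steps 2 to 4 use none.

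**1. The plan's own figure.** 3.5/9.2 = 0.380. This is a risk ratio; the odds ratio is (0.035/0.965)/(0.092/0.908) = 0.358. I used Hsieh's formula for logistic regression with a binary predictor:

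N = [z_α√(P(1−P)/B) + z_β√(p1(1−p1) + p2(1−p2)(1−B)/B)]² / [(p1−p2)²(1−B)]

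Here p1 = 0.092, p2 = 0.0371 (from odds ratio 0.38), B = 1/3 (an assumption: one arm of three), P = 0.0737 and z_α = z_β = 1.645. The result is N = 963, within 1.3% of 951. A Wald calculation upward from 3.5% with odds ratio 1/0.38 = 2.63 and the same share gives 949 to 951. So 951 is reproducible as a total for one binary contrast, but it does not show which direction was entered in the software.

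**2. Power in the tested direction.** Signed pooled z-test:

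power = Φ[(d − 1.645·se0)/se1], with d = p_long − p_2h, se0 = √(2p̄(1−p̄)/317) and se1 = √((p_2h(1−p_2h) + p_long(1−p_long))/317)

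- *Same 5.7 points, upward from 9.2% to 14.9%:* se0 = 0.02586, se1 = 0.02576. Φ[(0.057 − 0.04253)/0.02576] = Φ(0.56) = **0.71**. Power 0.95 would need 704 per arm.
- *Labels swapped, 2-h 3.5% and longer 9.2%:* se0 = 0.01937, se1 = 0.01924. Φ[(0.057 − 0.03186)/0.01924] = Φ(1.31) = **0.90**.
- *Literal planning effect, 2-h 9.2% and longer 3.5%:* Φ[(−0.057 − 0.03186)/0.01924] = Φ(−4.62), about 0.000002. This only confirms that effect and test lie in opposite tails.

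**3. Smallest detectable rise at 317 per arm** (same formula solved for p_long):

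| 2-h rate | power 0.80 | power 0.95 |
|---|---|---|
| 9.2% | 15.7% (OR 1.84) | 18.1% (OR 2.19) |
| 3.5% | 8.1% (OR 2.43) | 10.0% (OR 3.08) |

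**4. A smaller rise from the lower rate.** A doubling from 3.5% to 7.0% has power 0.63.

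**5. Clustering, for illustration.** Three homes per arm means about 317/3 = 105.7 residents per home. The document gives no intracluster correlation (ICC), so the values here are assumptions. The design effect is 1 + 104.7 × ICC.

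| assumed ICC | design effect | effective n per arm | power, 9.2% to 14.9% |
|---|---|---|---|
| 0.005 | 1.52 | 208 | 0.56 |
| 0.01 | 2.05 | 155 | 0.46 |
| 0.02 | 3.09 | 102 | 0.35 |

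These values still use normal quantiles. With three homes per arm, that flatters the result.

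**The case against.** **The direction is inferred.** The document never says that the 3-h or 4-h arm is expected at 3.5%, and the sample-size formula has no sign. A reader might infer that the software was run for a reduction; the documents do not show that, and a reciprocal labelling slip is possible. This stands, and it limits the point to what the text states. Relabelling does not rescue the text: it puts the 2-h arm at 3.5%, against the explicit 9.2% assumption, and two arms of 317 then have power 0.90. The shortfall from 0.95 arises in either tail, because 951 fits as a total for one contrast. It is not evidence about direction.

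**The trial is not blind to a difference of this size.** A reader might infer from the figure of 0.000002 that the trial could not detect its own planning effect. That goes too far. A test for harm should almost never reject when longer intervals reduce ulcers. The Quantitative analyses section also sets a two-sided 0.05 level, and both analysis sections use overlap of 95% confidence intervals; neither rule has a direction.

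**The 9.2% is openly an assumption.** A reader might conclude that it has been shown not to be a 2-h rate. It has not. The Risk and challenges section reports only what is thought to happen. The Background says that current protocols "recommend repositioning residents at moderate, high, and severe-risk every 2 h", without saying that nobody else is turned every 2 h. These passages call for reconciliation, not deletion of the assumption.

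**Error rate and estimates are unaffected.** That is true. The damage is to a power claim that the section relies on for its main conclusion.

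**Conclusion.** The sizing statement is wrong as written. The section quotes 0.95 power for a ratio below 1, with 9.2% tied to the 2-h arm, and declares a one-tailed test for a ratio above 1. Nothing elsewhere in the document reconciles the two. On the literal reading the effect lies in the wrong tail; on the shared-package reading it is not a between-arm effect.

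The 0.95 therefore gives no assurance against missed harm. Before clustering, a 5.7-point rise from 9.2% would be missed about 29% of the time (1 − 0.71). Power of 0.95 is reached only for a near doubling from 9.2% or a near tripling from 3.5%. These figures assume a pooled two-proportion z-test, 317 per arm, one-sided 0.05 and independent residents. Any positive correlation within homes makes them worse.

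**What to change.** Keep N and revise the Statistical power section.

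1. Withdraw the claim of 0.95 power at an odds ratio of 0.38.
2. Restate the sizing in the direction tested: an odds ratio above 1 for the longer interval against the 2-h arm.
3. Give the calculation over a stated range of 2-h rates for this trial's eligible residents, such as 3.5% to 9.2%.
4. Report the smallest detectable increase at each rate after a clustering allowance for three homes per arm, under a stated range of assumed intracluster correlations. Figures restated without that allowance would still be too favourable.
5. Reconcile the assumption that 9.2% reflects 2-h repositioning with the Risk and challenges statement that practice is thought to run beyond 2 h.

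The cost is a rewritten paragraph and a short recalculation. Recruitment, arms and analysis model do not change. The downside is a less favourable stated power, and so weaker support for reading a non-significant result as no increase.

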## Abstract

**Background:**

Pressure ulcers/injuries (PrUs), a critical concern for nursing homes (NH), are responsible for chronic wounds, amputations, septic infections, and premature deaths. PrUs occur most commonly in older adults and NH residence is a risk factor for their development, with at least one of every nine U.S. NH residents experiencing a PrU and many NHs having high incidence and prevalence rates, in some instances well over 20%. PrU direct treatment costs are greater than prevention costs, making prevention-focused protocols critical. Current PrU prevention protocols recommend repositioning residents at moderate, high, and severe risk every 2 h. The advent of visco-elastic (VE) high-density foam support-surfaces over the past decade may now make it possible to extend the repositioning interval to every 3 or 4 h without increasing PrU development. The TEAM-UP (Turn Everyone And Move for Ulcer Prevention) study aims to determine: 1) whether repositioning interval can be extended for NH residents without compromising PrU incidence and 2) how changes in medical severity interact with changes in risk level and repositioning schedule to predict PrU development.

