#### Analysis

##### Quantitative analyses.

We hypothesize that there will be no significant difference in PrU incidence between the 3 treatment arms in the study using three risk level groups: high risk (Braden Scale Score, 10–12), moderate risk (Braden Scale Score, 13–14), and low risk (Braden Scores > 14). The hypothesis of no group difference will be tested by examining whether the 95% confidence intervals of the rates of PrU and the 2-h repositioning overlap. If so, the hypothesis for no group difference will be confirmed. We will also determine how changes in medical severity components (as measured by a modified Comprehensive Severity Index), change in clinically assessed risk level (low, moderate, high as measured by the Braden Scale) and their interactions with repositioning schedule are associated with PrU development.

Descriptive statistics will be used to examine resident status, interventions, outcomes, and cost elements. For categorical variables, we will create contingency tables and use chi-squared or Fisher’s exact tests to determine the significance of bivariate differences. For continuous variables, we will use analysis of variance or non-parametric tests, depending on variable distributions. A two-sided *p*-value < 0.05 will be statistically significant. Intervention cost by NH and study arm and incremental cost-effectiveness ratios (ICERs) will be calculated and compared for cost per percentage reduction in PrUs. Sensitivity analysis will be conducted with the range of observed repositioning times, nurse salaries, and market prices for non-labor inputs to assess the robustness of the ICERs and their sensitivity to labor and non-labor input prices.

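### The named Aim 1 comparisons (4 h vs 2 h and 4 h vs 3 h) do not match the trial's own question, which also needs 3 h vs 2 h as a named test

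*Protocol article*

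**What the plan says.** All places are in the protocol article.

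- **Statistical power, Aim 1 tests.** Odds ratios from a logistic regression on the three arms are to test the difference "between the 4-h arm and the 2-h arm as well as between the 4-h arm and the 3-h arm at 4 weeks".
- **Statistical power, the remaining pair.** The sentence continues: "we are assuming that the distance between the 2-h arm and the TURN 3-h odds ratio will be larger". No test of this trial's 3-h arm against its 2-h arm is named.
- **Statistical power, decision rule.** The confidence-interval rule is applied to "the two pairs of compared groups (e.g., 4-h arm vs. 2-h arm and 4-h arm vs. 3-h arm) overlap".
- **Statistical power, reason for one tail.** "we are only interested in determining whether the PrU rate is higher for assigned repositioning intervals longer than the current 2-h standard practice".
- **Quantitative analyses.** The hypothesis is "no significant difference in PrU incidence between the 3 treatment arms in the study", and it "will be tested by examining whether the 95% confidence intervals of the rates of PrU and the 2-h repositioning overlap".
- **Abstract, Background.** The newer support surfaces "may now make it possible to extend the repositioning interval to every 3 or 4 h without increasing PrU development".

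**The concern.** The trial asks whether either longer interval raises incidence above the 2-h standard. Two comparisons answer that: 3 h vs 2 h and 4 h vs 2 h. The Statistical power section keeps the second, replaces the first with a comparison of two extended intervals, and bridges the gap with an assumption that refers to another trial's 3-h result.

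This matters most if 4 h turns out worse than 2 h. The 3-h interval is then the remaining candidate for extension, and the reader needs a pre-named comparison of 3 h with the standard. The named pairs would give 3 h against 4 h. A 3-h vs 2-h comparison brought in at that point could be challenged as chosen after the 4-h result was seen.

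**Working it through.** **1. The stated pairs against the stated question**

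| Comparison | Named Aim 1 test (Statistical power) | Covered by the one-tailed rationale (longer than 2 h vs 2 h) | Covered by a rule against 2 h (Quantitative analyses) | Needed for extending to 3 or 4 h (Abstract) |
|---|---|---|---|---|
| 4 h vs 2 h | yes | yes | yes | yes |
| 3 h vs 2 h | no | yes | yes, by implication | yes |
| 4 h vs 3 h | yes | no | no | no |

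The one-tailed rationale covers a pair that is not named, and a named pair falls outside that rationale. The assumption that the 2-h to 3-h distance is larger also fits poorly with a hypothesis of no difference among the three arms.

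**2. What can be recovered from the named pairs**

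On the log scale, log OR(3 h vs 2 h) = log OR(4 h vs 2 h) − log OR(4 h vs 3 h). The three-arm model therefore contains the point estimate. The two separate confidence intervals do not give its precision, because both odds ratios share the 4-h arm and their covariance is needed. What is missing is a named test with its own interval.

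**3. The plan's own sample size**

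Inputs from Statistical power: reference rate 9.2%, odds ratio 0.38, one-tailed 0.05, power 0.95, N = 951 (3 × 317).

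An odds ratio of 0.38 on 9.2% gives a second rate of 3.71%. The document does not state what share of the sample carries the binary predictor, so a share π = 1/3 is assumed here. The Hsieh formula, with p̄ = (2/3)(0.092) + (1/3)(0.0371) = 0.0737, is

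N = [1.645·√(p̄(1−p̄)/π) + 1.645·√(p₀q₀ + p₁q₁(1−π)/π)]² / [(p₀−p₁)²(1−π)]

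= (0.744 + 0.647)² / (0.0549² × 2/3) ≈ 963.

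Variants of the Demidenko method give 959 (share 1/3), 947 (share 2/3) and 924 (share 1/2). All lie within 3% of 951. The plan's figure thus reproduces as a total for one binary contrast over the whole sample.

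**4. Power of one pair, 317 vs 317, one-sided 0.05, clustering ignored**

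Power = Φ[(|p₁−p₂| − 1.645·SE₀)/SE₁], with SE₀ pooled and SE₁ unpooled.

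- 9.2% vs 3.5%: SE₀ = √(2 × 0.0635 × 0.9365/317) = 0.01937; SE₁ = √((0.092 × 0.908 + 0.035 × 0.965)/317) = 0.01924; (0.057 − 0.03186)/0.01924 = 1.307; power 0.904.
- 9.2% vs 3.71% (odds ratio 0.38): power 0.880.

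The formula depends only on the two rates and the two arm sizes. At the same rates, 3 h vs 2 h has the same power as either named pair.

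**5. If the error rate is shared across pairs (9.2% vs 3.5%)**

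- Two comparisons at one-sided 0.025 each: 0.839 per comparison.
- All three pairs at 0.05/3 each: 0.794 per comparison.

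**6. Illustration with assumed rates (not in the document)**

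Let 2 h be 3.5% and both longer intervals 7%. The 4-h vs 3-h difference is then 0, and the doubling at 3 h has no named test. Power for 3.5% vs 7% is Φ(0.035/0.01766 − 1.645) = Φ(0.337) = 0.63, for 4 h vs 2 h and equally for 3 h vs 2 h.

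Now let 3 h be 3.5%, as at 2 h, and only 4 h be 7%. The 4-h vs 3-h test still misses the difference with probability 1 − 0.63 = 0.37. A non-significant 4-h vs 3-h result therefore does not tell these two situations apart.

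**The case against.** The strongest reply is that 3 h is tested after all. The Quantitative analyses section states a hypothesis over all three arms and a rule against 2 h, which on an ordinary reading takes in 3 h vs 2 h. One logistic model on three arms yields that odds ratio with no further modelling. The second listing of pairs starts with an e.g. These points stand as far as they go. A reader might infer that 3 h is never tested, or that the trial cannot answer on 3 h, and the document does not support either reading. The e.g. adds little, since the phrase speaks of two pairs and the earlier sentence names the same two without it. The broader wording elsewhere leaves two sections describing different sets of comparisons.

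A second reply is that the pairs appear in a power section, and that the assumption may only explain the sizing: size on the contrasts expected to be smaller. That is a possible reading, but the sentence also states which differences are to be tested, and the decision rule reuses the same pairs.

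A third reply is that the two pairs inform each other, and that if 4 h is acceptable then 3 h follows. It would go too far to say that 4 h vs 3 h shows nothing. But the inference from 4 h to 3 h needs an ordering of risk by interval that the document does not state, and it gives no help when 4 h is worse.

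Finally, a condensed article may leave a full contrast list to the analysis plan. Here the article does list the pairs, and the point is that the list conflicts with its own text.

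**Conclusion.** The concern holds as a mismatch of specification. The named Aim 1 pairs omit 3 h vs 2 h and include a pair outside the one-tailed rationale. They differ from the rule against 2 h in Quantitative analyses and from the aim of extending to 3 or 4 h. The omitted contrast is estimable and loosely implied, but it is not a named Aim 1 test. If 4 h proves worse than 2 h, the named pairs do not directly judge 3 h against the standard.

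No power is gained by the present choice: 0.88 to 0.90 for any 317 vs 317 pair at the plan's own rates. These figures assume independent residents, one-sided 0.05 per pair and equal arms. Clustering in three homes per arm would lower the power of all pairs, and no design effect is applied here. The 3.5% vs 7% case is an illustration and carries no weight as evidence of the defect.

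**What to change.** By a dated and justified amendment before outcome analysis:

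1. Name 3 h vs 2 h and 4 h vs 2 h as the two Aim 1 comparisons, in the same words in Quantitative analyses and in Statistical power, including the decision rule.
2. Keep 4 h vs 3 h as a secondary comparison.
3. Remove the assumption about the 2-h to 3-h distance as a substitute for a test. If it was meant as a sizing argument, say so and keep it apart from the list of tests.
4. State whether the error rate is shared across the two comparisons.

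Keeping 4 h vs 3 h as a third Aim 1 test next to 3 h vs 2 h would also resolve the conflict, at the price of attention to multiplicity.

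The cost is an amendment and no more residents: the data and the number of Aim 1 comparisons stay the same. It is more than an edit of wording, because the article reports 3 of 9 homes already completed, so the date and the reason for the change must be on record.

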## Methods

The TEAM-UP study is a cluster randomized clinical trial with facility-level use of an assigned repositioning interval as the primary intervention and will be conducted at 9 NHs that are all using VE support surfaces. Each participating NH will be randomly assigned to one of three intervention arms. Each arm will have 3 NHs with each NH using a single, NH-wide repositioning interval at either 2, 3, or 4 h as standard of care during the 4-week intervention period. Randomization will occur at the facility level. The sequence in which the repositioning intervals are to be implemented will be randomly ordered and, then assigned to NHs inclusive of each arm of NHs. Thus, 3 clusters of 3 NHs are created with randomly sequenced repositioning intervals.

A secondary cluster is created within each NH as the NH implements its standard risk assessment protocol; residents will be clinically categorized forming clusters by level of risk for developing a new PrU. Level of risk categorization into 3 groups is defined by a Braden score of low (15–18), moderate (13–14), or high (10–12) [32]. All eligible residents will wear a wireless triaxial accelerometer sensor throughout the intervention as part of the NH’s standard of care. Residents may refuse the sensor and can decline to move when prompted by staff as part of their right to refuse care (see Fig. 1). This pragmatic approach offers a unique opportunity to study a single NH-wide repositioning schedule, thus avoiding the potential for staff confusion associated with resident-level random assignment to repositioning intervals, which would require staff to simultaneously execute multiple turning schedules.

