Because we will be examining PrU development from assessment to assessment, the rate of PrU incidence will be modeled as a binary outcome using repeated measures logistic regression and a specified working correlation matrix that models the correlation of responses within subjects. Full likelihood estimation methods are not appropriate for repeated measures logistic regression, so generalized estimating equations (GEEs) will be used instead with model fit assessed using the quasi-likelihood information criterion (QIC). Robust standard errors, clustered at the facility level, will be employed to account for covariance among residents within facilities over time. To test the robustness of models, we will also use non-linear mixed models using PROC GLIMMIX as another option for modeling the data (instead of GEEs using PROC GENMOD). With PROC GLIMMIX, we can use random effects to model the covariance rather than clustered standard errors. As predictors, we will include time-invariant resident characteristics, e.g., age, gender, Medicaid payer, and repositioning schedule, as well as time-varying characteristics, such as resident severity measure, risk level as determined by Braden Scale© score, staffing characteristics (e.g., number, mix, and turnover), and suggested MDS resident data elements as covariates. We may lag some time-varying resident characteristics by one assessment because we want to study the associations of repositioning time with PrU development, controlling for the starting point of the resident for that assessment interval. Interaction variables will be included in the predictor data set.

Residents without PrUs who drop out of the study after at least a three-day stay but before the conclusion of 4 weeks will be included in the analysis based on intent to treat. Residents who develop a Stage 3 or worse PrU, or deep purple discoloration, will be removed from the study per repositioning protocol, but will be considered a completed case if the ulcer developed on the coccyx, sacrum, trochanter or heel. Residents who develop ulcers on sites not thought to be influenced by bed position or limited mobility, or related to sitting, will continue to be followed for analysis, but will not be included in the NH-wide protocol.

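### The stated 0.95 power treats residents as individually randomised; with three nursing homes per arm it is not attained under any reading of the plan's figures

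*Protocol article*

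**What the plan says.** The Methods section fixes the design: "Randomization will occur at the facility level", and "Each arm will have 3 NHs with each NH using a single, NH-wide repositioning interval". The Quantitative analyses section plans GEE logistic regression and states that "Robust standard errors, clustered at the facility level, will be employed to account for covariance among residents within facilities over time", with a random-effects model as a robustness check.

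The Statistical power section sizes Aim 1 with a logistic regression of incidence on arm. The total of 951 residents, split equally into three groups of 317, is the number that "will be required to detect an odds ratio of .38 with a power of 0.95". The test is one-sided at 0.05, and the software named is G*Power. The contrasts named are 4-h versus 2-h and 4-h versus 3-h. The effect is 9.2% against 3.5%, a difference of 5.7 points. The section says that risk level is the only covariate that might need controlling and that the power analyses already cover it. It also reports that the nine homes were those "identified with the highest PrU incidence rates which averaged 9.2% (SD = 3.3". That SD is in percentage points, and it enters no calculation. The Aim 2 calculation is described with an autoregressive residual structure and no facility-level correlation.

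The same section explains why 0.95 was preferred to 0.80: a smaller Type II error is wanted because the authors expect not to reject the hypothesis of no difference.

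**The concern.** Residents of one home share staff, case mix and the assigned interval, so 317 residents in three homes carry less information than 317 independent residents. The analysis section recognises this and the power section does not. With three homes per arm, there are also few degrees of freedom from which to estimate the between-home variance.

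The figure carries more weight than a sample-size justification usually does. The plan sets no non-inferiority margin and will take overlapping confidence intervals as confirming no difference. High power is the protection it offers against reaching that conclusion by default. If the true Type II error is well above 0.05, that protection is weaker than stated.

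**Working it through.** **Inputs.** From Statistical power: rates 9.2% and 3.5%, difference 5.7 points, odds ratio 0.38, one-sided α 0.05, 317 per arm, SD 3.3 points across nine homes. From Methods: three homes per arm. Derived: 317/3 ≈ 106 residents per home.

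**1. Reproducing 0.95.** An odds ratio of 0.38 on 9.2% implies P2 = 3.71%. The Hsieh formula for logistic regression with a binary predictor of prevalence B is

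N = [z₀.₉₅√(P̄(1−P̄)/B) + z₀.₉₅√(P1(1−P1) + P2(1−P2)(1−B)/B)]² / [(P1−P2)²(1−B)], with P̄ = (1−B)P1 + B·P2.

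With B = 1/3 (one arm against the other two), N = 963, and power at N = 951 is 0.948. A Wald formula with variance correction gives 959 (B = 1/3) or 947 (B = 2/3). The article does not state B, so it is an assumption here. The match needs all 951 residents in one contrast and no clustering term.

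**2. The named contrast, still without clustering.** For 317 versus 317, the two-proportion formula gives power 0.904 (9.2% v 3.5%) or 0.880 (odds ratio 0.38). Power of 0.95 would need 394 or 431 per arm.

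**3. Home-level comparison, 3 v 3.** Take 3.3 points as the SD of observed home rates, equal in both arms:

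- SE = 3.3 × √(2/3) = 2.69 points
- noncentrality = 5.7/2.69 = 2.12
- one-sided power by noncentral t = 0.541 with 4 df (two arms) and 0.589 with 6 df (SD pooled over three arms)
- with a normal reference, 0.68

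**4. Other readings of the 3.3.** The binomial variance of a two-arm difference is (0.092×0.908 + 0.035×0.965)/317 = 0.000370, an SE of 1.92 points. If 3.3 contains sampling error at about 106 residents per home, the net SD is √(0.033² − 0.092×0.908/105.7) = 1.73 points. A proportional SD is scaled by 3.5/9.2 in the lower arm. Each SE below is the root of the between-home variance (the two arms' home variances summed, divided by 3) plus the binomial variance.

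| Reading | SE (points) | t, 4 to 6 df | Normal |
|---|---|---|---|
| 3.3 purely between homes, equal | 3.31 | 0.41 to 0.45 | 0.53 |
| 3.3 purely between homes, proportional | 2.80 | 0.52 to 0.56 | 0.65 |
| Net 1.73, equal | 2.39 | 0.63 to 0.68 | 0.77 |
| Net 1.73, proportional | 2.20 | 0.69 to 0.74 | 0.83 |
| Zero between-home variance | 1.92 | 0.78 to 0.83 | 0.91 |

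**5. Assumed ICCs** (not from the document), design effect 1 + (105.7−1)×ICC. ICC 0.01 gives a design effect of 2.05 and power 0.53 to 0.57 (4 to 6 df). ICC 0.05 gives 6.23 and 0.26 to 0.28.

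**6. Simulation.** A beta-binomial simulation of the home-level t test with 4 df gave 0.47, 0.52, 0.64, 0.70 and 0.79 for the five rows of the table in order. This agrees with the analytic values to within about 0.06.

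**The case against.** No other part of the article handles this, and no reading restores 0.95. The fair objections concern how far the point can be pushed.

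- **One might infer that the true power is 0.54 to 0.59.** The article does not support that precision. It gives neither the period nor the denominators behind the SD, and the homes were chosen for high rates. The pair of figures needs 3.3 to include sampling error at trial-size denominators and to be as large in the 3.5% arm. This objection stands, so the range must be shown.
- **The t test on home rates is not the planned analysis.** The plan uses GEE with facility-clustered robust errors. The NH-level data section also intends facility characteristics, including baseline incidence, as covariates, which could reduce between-home variance at a cost in degrees of freedom. A small-df reference is defensible because a normal one is anti-conservative with nine clusters, but it is a choice and should be labelled as one.
- **One might blame the whole shortfall on clustering.** Part of it comes from the contrast (step 2) and part from the few degrees of freedom (zero-variance row).
- **One might infer that a non-significant result would say almost nothing.** That goes too far. The facility-clustered errors would carry the clustering into the confidence intervals, which remain informative about size. Treating overlap as confirmation is a separate weakness that even a true 0.95 would not cure.

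**Conclusion.** The concern holds in this form: 0.95 is a resident-level figure attached to a design with three randomised homes per arm, and it is overstated under every reading tried. Between 0.54 and 0.59 is the direct result if 3.3 points is the SD of observed home rates, equal in both arms, with a t reference on 4 to 6 df. Given what the article leaves open about that SD, the supportable statement is about 0.41 to 0.74 with a t reference, or 0.53 to 0.83 with a normal one. The Type II error for a 5.7-point difference is then about 0.26 to 0.59 (t), not 0.05. Confidence is high that power is below 0.95 and much lower for any single value. The analysis plan itself does allow for clustering. The fault lies in the power statement and the inference rested on it.

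**What to change.** In the Statistical power section, replace 0.95 with cluster-adjusted power, or a detectable difference, for the 4-h v 2-h and 4-h v 3-h contrasts. State three homes per arm, about 106 residents per home, the SD or ICC range with the period and denominators behind it, whether the SD is taken as equal or proportional to the rate, and the reference distribution with its df. On the present figures this is roughly 0.4 to 0.75 with a t reference. As a detectable difference at 0.80 power with an SE of 2.69 points, it is approximately (1.943 + 0.906) × 2.69 = 7.7 points with 6 df, or (2.132 + 0.941) × 2.69 = 8.3 with 4 df.

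Delete the sentence that relies on 0.95 power to support a no-difference conclusion.

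The cost is restated figures in one section and a less favourable power claim. The number of homes and the enrolment target stay as they are.
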